**4.10 Outcome Measures** **(Quantitative)**

***Primary Outcome Measures***

***Acceptability:*** Operationalised in terms of acceptability of the intervention. The proportion of pupils who complete all agreed sessions will be recorded (>60% excellent. 40%-60% acceptable; <40% not acceptable) on the Reframe IT-UK website. Acceptability of the suicide prevention lesson, including whether or not participants thought it was “useful”, “interesting”, or “upsetting”, will be assessed at T2 only using purpose designed items. Participant views on the Reframe IT-UK intervention will be assessed at T3.

***Social validity:*** We will test this through a process evaluation using bespoke quantitative surveys following the delivery of each component of the MAPSS programme at T2 and T3. We will also conduct qualitative interviews with staff and focus groups with pupils across the study period.

***Feasibility of the trial:*** We will collect data on: 1) the missing data on completed assessment (<15%); 2) change or variability on outcome measures (e.g., suicide ideation, depressive or hopelessness symptoms); and, 3) whether schools implemented and supported the accessibility of the online intervention.

***Secondary Outcome Measures***

The secondary outcomes for this study are:

1. Change in **past four-week suicidal ideation** at T3 and T4, compared to T2, assessed via the SIDAS.^33^ The SIDAS is a self-report measure designed to screen individuals in the community for presence of suicidal thoughts and assess the severity of these thoughts.
2. Change in **symptoms of depression** at T3 and T4, compared to T2 and T1, will be assessed using the Patient Health Questionnaire – 9 item version.^43^
3. Changes in **hopelessness** at T3 and T4, compared to T2, will be assessed using the Brief-H-Pos, a 2-item positively worded measure of hopelessness.^44^
4. Differences in **health service use** and other resource use (education and local authority) comparing intervention and control group at T2, T3 and T4, will be assessed using a bespoke questionnaire adapted from the Young Mind Matters Service Use questionnaire.^45^
5. Purposefully designed questions on **intentions to seek help from informal sources**.
6. Change in **health-related quality of life** during the trial (T1, T2, T3, T4) will be assessed using the Child Health Utility–9 (CHU9D).^46^ The CHU9D can be used to derive quality-adjusted life years (QALYs). These data will be used in combination with data from 3) above, to assess the feasibility of the full economic evaluation.
7. Change in **suicide literacy** at T2, T3 and T4, compared to T1, will be assessed using an adapted version of the Literacy of Suicide Scale (LOSS).^47^

School staff (key contact or safeguarding lead) will complete a usual practice survey at T1 and T4, to ascertain current provision (i.e., establish a clear counterfactual), identify the level of programme differentiation, and to account for any potential compensatory rivalry or contamination in control schools.

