**3. Research Question**

Research question: What is the feasibility of a school-based suicide prevention programme comprising universal, selective, and indicated components in reducing suicide risk, improving risk recognition, and increasing health service use among young people aged 14-15 years in Northwest England?

MAPSS involves the delivery and evaluation of universal psychoeducation workshops (e.g., safeTALK) to school pupils, screening pupils for suicide risk (universal and selective approaches), and online CBT (Reframe IT-UK) delivered to pupils identified as being at-risk (indicated approach).

The primary aims of this study are to assess:

1. The acceptability and safety of conducting a trial of a suicide prevention programme in a school setting, operationalised in terms of adverse events and self-reported adverse consequences at post-intervention assessments.
2. The social validity (feasibility, utility, and acceptability) and implementation (including fidelity, quality, and dosage) of the MAPSS intervention, through a process evaluation consisting of bespoke quantitative surveys and qualitative interviews and focus groups.
3. The feasibility of delivering a large-scale, appropriately powered, cluster-RCT with economic evaluation in the future, including assessment of recruitment methods, retention rates, and outcome measures-and to assess links between these short-term trial outcomes and longer terms costs and outcomes.

We aim to test the following as secondary outcomes:

1. Comparison of suicide literacy and help-seeking intentions for suicidal thoughts or behaviours between the control group and pupils attending the suicide prevention workshop.
2. The identification of pupils at-risk of suicide who had not previously sought help.
3. Comparison of suicidal ideation, depression, and hopelessness between the control group and pupils in the Reframe IT-UK intervention group.
4. Rates of health-service use to inform an economic evaluation - levels of health-related quality of life.
5. Help-seeking intentions from informal sources.

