**4. Research Plan/Methods**

**4.1 Design and Theoretical/Conceptual Framework**

The study will be conducted over a 2-year period (Jan 2024-Jan 2026), with 3 months for set up, 18 months feasibility, and 3 months consolidation.

This study adopts a multiphase feasibility design, consisting of 3 work packages (WP):

**WP1:** A three-month set-up stage to: i) make any adjustments to the interventions as determined from the pilot study, ii) recruit the RA, and iii) spend dedicated time recruiting schools from a diverse range of backgrounds, with two schools recruited in the first 3 months and the remaining four schools within 9 months, to enable alignment with school academic terms.

**WP2:** An 18-month feasibility study evaluating MAPSS in 6 schools: a feasibility cluster-RCT (schools as the unit of randomisation). Four schools will be randomised to receive MAPSS (intervention arm) and two schools will be randomised to continue with usual practice (control arm). Surveys will be completed by both arms at all timepoints. The trial will include i) baseline survey, ii) universal suicide prevention lesson (e.g., safeTALK) in intervention arm, iii) survey and screening 2 weeks after suicide prevention lesson, iv) an indicated Reframe IT-UK CBT intervention in intervention arm for pupils identified as high suicide risk, and usual care in control arm v) survey 2-weeks after Reframe IT-UK CBT, vi) survey 12-months post baseline.

**WP3.** A parallel process evaluation, to establish perceptions of social validity of the programme for use in the UK, and the appropriateness of the research design for effectiveness trials.

The study is facilitated by an extensive partnership with Local Authorities, schools, public advisors, professional educators, and researchers (see Letters of Support attached from collaborators and partner organisations). The specific objectives are to assess:

1. The acceptability and safety of a suicide prevention programme in schools

A mixed-methods approach will be used to determine acceptability and safety of trialling a suicide prevention programme in UK schools. The proportion of pupils who complete all agreed sessions of therapy will be recorded (>60% excellent; 40%-60% acceptable; <40% not acceptable).

Safety will be operationalised in terms of adverse events linked to the intervention (e.g., suicidal behaviour, crises, or increased self-harm), and in terms of self-reported adverse consequences at post-intervention assessments.

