**4.3 Planned intervention**

The training in schools for pupils, teachers, and parents will be funded by suicide prevention commissioners within the Local Authority (see Director of Public Health Letter).

1) A minimum of 6 staff from each school will receive training from Papyrus: **Suicide Prevention – Overview Tutorial (SP-OT)**, to ensure staff are equipped to manage any risk identified from the screening. SP-OT is delivered in a single session over 1.5 hours online. Papyrus will also provide an online information session, **Suicide Prevention - Awareness, Resource, Knowledge (SP-ARK),** along with support packs, for parents of all children in Year 10 at each participating school. #MyGPGuide; a guide for CYP with lived experience of self-harm and suicidality will be shared with schools and families.^31^

2) **Suicide prevention lesson** such as safeTALK, developed by LivingWorks Education,^32^ a suicide alertness training workshop suitable for anyone over the age of 14. The lesson comprises a single 3.5-hour face-to-face workshop, designed to help participants understand suicide warning signs in themselves and others, gain knowledge about sources of support, apply basic ‘TALK’ steps (Tell, Ask, Listen, and KeepSafe), and signpost others. Suicide prevention lessons will be delivered by trained Suicide Prevention Facilitators at Grassroots Suicide Prevention to classroom-sized groups of pupils (maximum 30 pupils per session with at least one teacher present).

3) The **screening** will take the form of self-report measures embedded into the questionnaires at each timepoint. Researchers will inform each school after each timepoint of any pupils who are assessed to be at risk. Pupils who report suicidal ideation within the past four weeks (Suicide Ideation Attributes Scale [SIDAS] score of 21 or higher)^33^ or any level of current suicidal ideation (single multiple-choice item) will be flagged by the research team and followed up by the school safeguarding lead.

4) **Reframe IT-UK** has been adapted from the Reframe-IT intervention developed in Australia.^17,27^ It comprises eight 20-minute online self-guided CBT modules, following the stories of two young people who make video diaries about their day-to-day life and their experience of feeling suicidal. There is also a message board through which the participants can communicate with a moderator, a mood diary, and signposting information.

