**4.7 Overview of Research Methods**

***Quantitative Data Collection***

Participants will complete a suite of quantitative measures (see details below) online in school at 4 time-points: baseline (T1); 2-4 weeks post-baseline (after suicide prevention lesson; T2); 12 weeks post-baseline (after Reframe IT-UK; T3); and 1-year post-baseline (T4). The survey system will flag participants who score in the at-risk range for suicidal ideation.^33^ The research team will then contact the school about these pupils to determine eligibility for participation in the Reframe IT-UK in intervention schools. Eligible pupils will then be offered the intervention and TAU. Pupils receiving the Reframe IT-UK intervention will complete the 8 modules in the 10 weeks between T2 and T3 (i.e., approximately one module per week). Primary outcomes will be measured at T2 for suicide prevention lesson and T4 for Reframe IT-UK.

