**4.9 Randomisation**

The unit of randomisation is the schools. After baseline data collection is complete, 6 schools will be randomised to one of two study groups. We will be comparing both arms to test which, if any, is better. To create balance in terms of deprivation, ethnicity, rurality and educational outcomes, a minimisation algorithm will be used at an intervention-to-control ratio of 2:1 across Cheshire and Merseyside. Two schools will be allocated to the control arm and four schools will be allocated to the intervention arm by a university statistician, who is independent of the study and blind to school identities. Methods of allocation concealment and randomisation processes will follow CONSORT^42^ (see figure 1). Schools will be randomised to receive a suicide prevention lesson (e.g., safeTALK) and Reframe IT-UK and TAU, or TAU only, via a random sequence generation computer algorithm. The method of randomisation will be conducted using a routine within STATA to generate (stratified) randomised (block sizes of 2, 4 and 6) allocations. Researchers completing study assessments will be masked to intervention allocation. The trial will follow an Intent-To-Treat (ITT) protocol. Attrition will be recorded and reasons for drop-out recorded where possible. Guidance will be sought from the advisory groups on how to manage and minimise attrition over the study period.

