**4.12 Data and Statistical Analysis**

***Quantitative Data Analysis***

Changes in primary and secondary outcomes over time will be assessed for pupils clustered within schools and the treatment group included as a fixed factor. The analysis will adopt the intention-to-treat approach. As a secondary analysis, compliance (as measured by the number of modules completed) and other potential covariates (e.g., gender) will be accounted for. If the amount of missing data is non-trivial, multiple imputation will be used. We will follow the recently published extension to CONSORT^42^ when reporting the results of this feasibility trial. We will calculate and present in a CONSORT flow chart:

- - 1. The proportion of young people with suicide ideation consenting to the study;
    2. The proportion completing baseline assessment and entering the randomised phase;
    3. The number of online modules used and the proportion completing all sessions;
    4. The proportion completing follow-up assessments at 12-weeks and one-year post-randomisation.

As this is a feasibility study, no formal hypothesis testing will take place. Quantitative data will be reported using summary statistics and 95% confidence intervals. We will compare the continuous scores on the SIDAS outcome measure graphically to assess between group trends. The SD of the primary outcome will inform the sample size calculation for the large-scale RCT.

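### Ideation and hopelessness are referenced to T2, and screening for Reframe IT-UK follows the lesson, so any lesson effect on T2 responses distorts the arm contrast

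*Protocol*

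**What the plan says.** Section 4.9 of the protocol fixes when allocation happens: "After baseline data collection is complete, 6 schools will be randomised to one of two study groups". T1 is therefore the only measurement before randomisation. The same section allocates schools to the lesson and Reframe IT-UK together, or to usual care, and promises intention-to-treat; section 4.12 repeats that and enters treatment group as a fixed factor.

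Section 4.1 gives the order of events: baseline survey, lesson in the intervention arm, then "iii) survey and screening 2 weeks after suicide prevention lesson", then Reframe IT-UK for pupils found to be at high risk, with usual care in the control arm. Section 4.7 puts T2 after the lesson and runs the modules between T2 and T3.

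Section 4.10 takes ideation "at T3 and T4, compared to T2, assessed via the SIDAS", gives hopelessness the same T2-only reference, and refers depression to both T2 and T1. Section 3 states the intended contrast: "Comparison of suicidal ideation, depression, and hopelessness between the control group and pupils in the Reframe IT-UK intervention group".

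Section 4.3 says that the screening "will take the form of self-report measures embedded into the questionnaires at each timepoint", so a T1 SIDAS score exists.

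**The concern.** T2 is not a baseline for the randomised comparison. It is taken after allocation, when one arm has had the lesson and the other has not. By section 4.3 the lesson aims to help pupils recognise warning signs in themselves as well as others, and the research question includes better risk recognition. A change in T2 self-report is therefore something that the protocol itself makes plausible.

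Two things follow if such a change occurs. First, pupils flagged after the lesson are a different slice of the year group in the two arms; this applies to ideation, hopelessness and depression alike. Second, change from T2 subtracts the lesson's effect in the intervention arm only. A lasting effect drops out of the contrast, and a temporary one reappears as later change with the opposite sign. A short-lived rise in reported ideation after the lesson would look like improvement by T3, which is unwelcome in a trial with safety among its primary aims. This second problem does not extend to depression, which also has a T1 reference.

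At stake are the reported secondary estimates with their confidence intervals, and an outcome definition that a definitive trial might inherit.

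**Working it through.** **Plan's own figure.** Section 4.8 expects 10% of pupils in the at-risk range. Section 4.6 gives about 810 pupils, 540 of them in lesson schools. Then 0.10 × 540 = 54 and 0.10 × (810 − 540) = 27, matching the stated 54 and 27. The match requires the same 10% in both arms, that is, no lesson effect on flagging.

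**Assumptions (not document figures).** The score is standard normal, with the cut-off at the control arm's 90th percentile, c = 1.2816. The lesson shifts T2 by d SD. The T2–T3 correlation ρ is 0.5 to 0.7. The effect of Reframe IT-UK is zero.

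**Formulas.**
- Share flagged in the intervention arm: p = 1 − Φ(c − d).
- With λ(x) = φ(x) / (1 − Φ(x)), the contrast in change from T2 among flagged pupils (intervention minus control) is (1 − ρ)[λ(c) − λ(c − d)] if the shift persists to T3.
- It is that quantity minus d if the shift has gone by T3.

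**Example, d = +0.2, ρ = 0.6.** λ(1.2816) = 1.755 and λ(1.0816) = 1.591. Persistent: 0.4 × (1.755 − 1.591) = +0.07. Transient: 0.066 − 0.2 = −0.13. The flagged groups also differ before allocation: their mean T1 score is ρλ, so 0.6 × 1.591 = 0.95 against 0.6 × 1.755 = 1.05.

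| Lesson shift d (SD) | Flagged, intervention | Pupils, intervention (control 27) | Contrast, persistent shift | Contrast, transient shift |
|---|---|---|---|---|
| −0.3 | 5.7% | 31 | −0.08 to −0.13 | +0.17 to +0.22 |
| −0.2 | 6.9% | 37 | −0.05 to −0.08 | +0.12 to +0.15 |
| 0 | 10.0% | 54 | 0 | 0 |
| +0.2 | 14.0% | 75 | +0.05 to +0.08 | −0.12 to −0.15 |
| +0.3 | 16.3% | 88 | +0.07 to +0.12 | −0.18 to −0.23 |

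Ranges are over ρ = 0.5 to 0.7. A simulation with 4 million draws at ρ = 0.6 and d = ±0.2 agrees.

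**Same cases with T1 selection and T1 reference (ρ = 0.6, d = ±0.2).** The T3 contrast is 0.00 if the shift is transient and ±0.20 if it persists. Both are the true effect of the randomised package at T3. The T2-based contrast misses that effect by 0.13 in either case: 0.20 − 0.07 = 0.13 if persistent, and 0.13 − 0.00 = 0.13 if transient.

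**The case against.** Reframe IT-UK runs between T2 and T3, so T2 is the natural pre-treatment score for the CBT component. If the lesson's effect persists and the CBT does nothing, zero is the right answer for the CBT. In that case the T2-based figure (0.07 SD) is closer to zero than the T1-based one (0.20 SD). This stands: the T2 reference is wrong for the package, not for every question. But the package is what was randomised, and the T2-based contrast is biased for the CBT component as well once flagging differs by arm or the lesson effect fades.

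The lesson effect is unknown and may be nil. SIDAS recalls four weeks, so a survey two weeks after the lesson partly covers the time before it; that limits change in actual ideation more than change in recognition or disclosure. Precision is also low: with 54 against 27 pupils and unit SD, the 95% half-width is 1.96 × √(1/54 + 1/27) = 0.46 SD before clustering and attrition.

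A reader might infer more than the document supports:

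- *That a biased arm difference feeds the definitive trial's sample size or the decision to proceed.* Section 4.12 carries forward a standard deviation and rules out hypothesis tests, the outcomes are secondary, and no criterion in Table 1 uses an arm contrast.
- *That eligibility is firmly fixed at T2.* Section 4.1 points that way, but section 4.3 screens at every survey, and sections 4.6 and 4.7 do not name the qualifying one. The T2 reference itself is explicit.
- *That the comparison is limited to pupils who used Reframe IT-UK.* Section 3 can be read that way, but its wording can also mean pupils as allocated, and section 4.6 speaks of an offer.
- *That adjusting for modules completed is a further error.* Section 4.12 says only that "compliance (as measured by the number of modules completed) and other potential covariates (e.g., gender) will be accounted for", as a secondary analysis and without a method. That detail can be left to the analysis plan.

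**Conclusion.** The point holds and should be fixed. The T2-only reference for ideation and hopelessness is explicit, and the order of events in section 4.1 puts selection after the lesson for all three outcomes. The resulting contrast conditions on something that allocation can alter, so it is not the intention-to-treat comparison of lesson plus Reframe IT-UK.

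With no Reframe IT-UK effect, the spurious contrast is roughly 0.05 to 0.23 SD for assumed lesson shifts of 0.2 to 0.3 SD, and zero if the lesson leaves T2 responses unchanged. These sizes rest on assumed shifts, assumed correlations and a normal score; the direction depends on the sign of the shift and on whether it lasts. The damage is confined to descriptive secondary estimates, their intervals and the outcome definition that a later trial might adopt. No progression decision depends on it.

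**What to change.** - **Sections 4.10 and 4.12:** make the randomised arm contrast at T3 and T4 T1-referenced, with the T1 score as covariate, for SIDAS, PHQ-9 and hopelessness. Use an at-risk set defined from T1 responses by the same rule in both arms, regardless of uptake. State that this estimates the effect of the lesson-plus-Reframe IT-UK package.
- **Same sections:** keep the contrast in T2-flagged pupils with the T2 reference, labelled as a descriptive, non-randomised look at the CBT component.
- **Section 3, secondary aim 3:** reword to compare arms as allocated.
- **Hopelessness:** confirm that the Brief-H-Pos is collected at T1. Section 4.7 describes a suite of measures at four timepoints, but section 4.10 does not name T1 for this scale.

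The cost is wording. T1 SIDAS is already in the survey by section 4.3, and section 4.10 already uses T1 for depression; only T1 hopelessness needs checking. The downside is real but small: the T1-defined set will include some pupils never offered Reframe IT-UK, and the contrast includes the lesson effect, so it does not isolate the CBT component. Keeping the T2-based description covers that question as far as this design allows.

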**4.11 Methods for Data Collection**

***Quantitative Data Collection***

Surveys will be completed online during school time by pupils. Schools will be asked to book an IT room for pupils to complete the surveys and will be provided with a detailed support pack for completing the measures with pupils, including links to the surveys, age-appropriate lesson plans, PowerPoint slides, and glossary. Surveys will not be anonymous as pupils will need to be monitored for risk and screened for potential participation in Reframe IT-UK. Thus, data linkage across time points will not be an issue. A ‘usual practice’ survey will be completed at T1 by one staff member at each school, to determine what ‘usual care’ looks like, and levels of program differentiation.

***Qualitative Data Collection***

As part of the qualitative process evaluation, case study fieldwork visits will be conducted at T2 (after suicide prevention lesson) and T3 (after Reframe IT-UK). We will use semi-structured interviews with school staff and intervention deliverers (N=3 per school x 2 visits = 8 interviews), and interviews (for Reframe IT-UK) and focus groups (for suicide prevention lesson) with pupils (N=1 per school x 1 visit = 4 focus groups; N=2 per school x 1 visit = 8 interviews), as well as observations and document analysis of intervention delivery.

Class teachers and members of the senior leadership (e.g., safeguarding leads) will be interviewed individually at each case study visit. Small groups (n=4-6) of pupils will participate in semi-structured focus groups regarding suicide prevention lesson (to reduce power imbalances and ease nerves), and one-to-one interviews (with a teacher present if requested) will be conducted with pupils who have taken part in Reframe IT-UK (due to the sensitive and personal nature of intervention participation). Bespoke semi-structured interview schedules have been developed for each key stakeholder group. All interviews/focus groups will cover trial feasibility and acceptability, and factors affecting implementation; overarching this will be a social validity framework.^48^ However, each schedule will be tailored to the relevant time point and stakeholder group. Prompts and probes will be utilised where necessary to clarify unclear responses and elicit further detail. Interviews and focus groups will be conducted in private and quiet parts of the school, and fully informed consent will be ensured.

Professionals who delivered the interventions in the case study schools will also be invited to be interviewed, to ascertain fidelity, quality, and dosage, and gain their perspectives on participant engagement and reach, as well as the feasibility of an efficacy trial. Interviews will be conducted at a time and place to suit them (face-to-face or online). Observations and document analysis will be arranged where possible with the intervention deliverers for additional context. All interviews/focus groups will be audio recorded and transcribed verbatim.

